### Outcomes

#### Main outcome

difference (%) in NHS prescription of drugs under scrutiny (expressed as DDD per thousand inhabitants/day), comparing those who have/do not have received the specific information. In case of relevant baseline unbalances, statistical adjustment will be sought

#### Secondary outcomes

• difference in the % of patients who were prescribed the specific drug(s)

• difference in the % of patients who were prescribed the specific drug(s) for the first time (in the previous 12 months)

• difference in expenditure for the specific drug (per 1000 patients/day)

• difference in NHS prescription of drugs under scrutiny (expressed as DDD per thousand inhabitants/day), comparing those who have received the "traditional" vs "enriched" format, and any information vs no information (Sardinia study only)

• differences in the main and secondary outcomes in each of the regions involved (cluster study only);

• differences in the main and secondary outcomes according to the n. of assisted population in the related PCG (cluster study only)

• differences in the main and secondary outcomes according to the terziles of physicians age

• adjusted difference in prescribed DDD per 1000 patients/day according to a statistical model, considering as possible covariates: overall prescription in DDD per 1000 patients day at baseline; n. of physicians in the specific PCGs; n. of assisted population; region (Emilia-Romagna or Friuli Venezia Giulia); geographical location (mountain, hill, plain, urban centre – according to definitions given by the Italian Statistics Institute); age distribution of assisted population (in quartiles); % females in the assisted population; physician age; total physician drug expenditure (excluding drugs under scrutiny); % assisted population with polyprescription (≥ three drugs of different classes); n. new prescriptions (in the last 12 months); month of evaluation; participation to the information meetings; % exact answers to the questionnaire testing knowledge (see additional file 1);

• difference in the variability (expressed as standard deviations) of prescription of drugs under scrutiny within PCGs (cluster study only)

• difference in knowledge (measured through the n. of correct answers to a specific anonymous questionnaire, see additional file)

• difference in attitudes (measured through the answers to a specific questionnaire, see additional file)

Drugs whose NHS prescription will be considered for the first two topic chosen are specified here below:

1. for benign prostatic hyperplasia, the main indicators will be: difference in the prescription of 5 alpha-reductase inhibitors (finasteride and dutasteride, for which a reduction is expected); and difference in the ratio between the prescription of alpha blockers terazosin plus tamsulosin (already off patent drugs) versus other drugs of the same classes available in Italy (alfuzosin plus doxazosin – an increase of this ratio is expected). Secondary indicators will be: difference in the prescription of each of the alpha blockers listed above (a reduction is expected); difference of concomitant prescription of 5 alpha-reductase inhibitors and alpha blockers; and overall difference in expenditure for either 5 alpha-reductase inhibitors or alpha blockers (a reduction is expected for both of these indicators).

2. for the primary prevention of osteoporotic fractures, the main indicators will be: difference in the prescription of either alendronic acid or of sodium risedronate (a reduced increase is expected for both of these indicators, especially for the latter – for which the generic form is still unavailable). Secondary indicators will be: difference in the prescription of raloxifene and strontium ranelate (a reduction is expected for both of these indicators); and difference in the ratio between the prescription of alendronic acid (already off patent) versus the other two oral bisphosphonates available in Italy (sodium risedronate and ibandronic acid – an increase of this ratio is expected)

Physicians' expectations, perceived barriers and the added value about the proposed intervention will be eventually evaluated through focus groups with a sample of participating doctors for each region (at the end of the spring and the autumn rounds).

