### Information retrieval

Monthly prescription data will be retrieved from provincial drug prescription databases. Although impossible to eliminate completely, information bias due to database accuracy should not affect our evaluation significantly, since limited error rates are expected.

In the cluster RCT, knowledge and attitudes of physicians will be evaluated through separate questionnaires distributed during the information meetings. Each set of questions will be topic dependent, therefore questionnaires will be developed for each topic. The additional file shows the questionnaires related to the first two topics.

The knowledge questionnaire will be 'nominal' and filling up it will be necessary for receiving CME credits, while the attitude questionnaire will be anonymous so that responders can express their views freely.

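### The secondary adjusted difference in DDD lists two post-randomisation variables, meeting participation and knowledge score, as possible covariates

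*Protocol article*

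**What the plan says.** The Secondary outcomes section lists an "adjusted difference in prescribed DDD per 1000 patients/day according to a statistical model, considering as possible covariates". The list that follows mixes several kinds of variable:

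- One covariate is expressly tied to baseline: "overall prescription in DDD per 1000 patients day at baseline".
- One has a look-back window with no anchor date: "n. new prescriptions (in the last 12 months); month of evaluation".
- Two can exist only after allocation: "participation to the information meetings; % exact answers to the questionnaire testing knowledge".

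The same section makes knowledge an outcome: "difference in knowledge (measured through the n. of correct answers to a specific anonymous questionnaire, see additional file". For the cluster trial, Information retrieval says that "knowledge and attitudes of physicians will be evaluated through separate questionnaires distributed during the information meetings".

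The main outcome is defined separately. Under Main outcome and Statistical analysis it is compared by intention to treat, whether or not the physician took part, and is adjusted only if relevant baseline imbalances appear.

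**The concern.** An adjusted between-group difference is normally read as a more precise estimate of the same effect that the unadjusted comparison targets. That reading holds when every covariate is fixed before randomisation. It fails when a covariate is something the intervention changes.

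Knowledge is such a variable. Changing it is one of the study's stated objectives, and it is a plausible route from meeting to prescribing. Holding it constant subtracts whatever part of the effect travels through it.

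Participation also follows randomisation. Depending on its coding, it may be nearly the same thing as receiving the intervention. Those who attend may also differ from those who do not.

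At stake is the meaning of one named secondary result. The article itself calls a 10% or 15% difference ambitious, so an adjusted figure that has lost a quarter or more of the effect could be misread as weak evidence for the programme.

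**Working it through.** The article gives no figure for the adjusted difference, so there is none to reproduce. The check asks what the arm coefficient becomes once each variable is added.

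**Inputs from the article.** Effect τ = −10% (Sample size estimates). About 150 PCGs and about 2000 GPs, so 2000/150 ≈ 13 GPs per PCG. ICC 0.08 (Table 2, finasteride + dutasteride). Both arms of the cluster trial are offered a meeting, each on a different topic (Intervention/Exposure).

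**Assumptions, not in the article.** Coefficient of variation 0.45, which affects noise and not the expected coefficient. A knowledge gain of 15 points with SD 15, and a score available in both arms. Attendance a of 60% or 80%, equal in both arms. A share p of the effect running through knowledge, from 0 to 100%. Attendance is generated with no link to prescribing other than through the intervention, so confounding by who attends is not simulated.

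**Expected arm coefficient.**

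1. Adjusting for knowledge: the direct part remains, τ(1 − p). For p = 25%, 50%, 75% this is −10% × 0.75 = −7.5%, −10% × 0.50 = −5.0%, −10% × 0.25 = −2.5%.
2. Adjusting for attendance at this topic's meeting, when the effect acts only in attenders: the attenders' effect is τ/a (−16.7% at a = 60%, −12.5% at a = 80%). The attendance term absorbs all of it, so the arm coefficient is 0.
3. Adjusting for attendance at whichever meeting was offered: the arm difference is τ/a in attenders and 0 in non-attenders. Its average is a × τ/a = τ = −10%.

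**Simulation** (600 runs per row, ordinary least squares on arm with and without the covariate):

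| Covariate added | Expected | Arm coefficient with covariate | Same runs, arm only |
|---|---|---|---|
| Knowledge, p = 0 | −10.0% | −9.94% | −9.94% |
| Knowledge, p = 25% | −7.5% | −7.32% | −9.87% |
| Knowledge, p = 50% | −5.0% | −4.86% | −9.86% |
| Knowledge, p = 75% | −2.5% | −2.55% | −10.10% |
| Knowledge, p = 100% | 0% | +0.27% | −9.79% |
| This topic's meeting, a = 60% | 0% | +0.08% | −9.87% |
| This topic's meeting, a = 80% | 0% | −0.45% | −10.33% |
| Any offered meeting, a = 60% | −10.0% | −9.88% | −9.89% |
| Any offered meeting, a = 80% | −10.0% | −10.05% | −10.06% |

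The simulated values follow the algebra closely. Without these covariates the model recovers about −10% in every row.

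**New prescriptions.** The covariate "n. new prescriptions (in the last 12 months" closely matches a listed outcome, "difference in the % of patients who were prescribed the specific drug(s) for the first time (in the previous 12 months". Evaluations fall six and 12 months after the intervention (Follow-up). A 12-month window ending at the six-month evaluation would cover 12 − 6 = 6 months before the intervention and six after. One ending at the 12-month evaluation would lie wholly after it. One ending before the intervention would be a legitimate baseline covariate. The article does not say which is meant.

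**Linkage.** Secondary outcomes calls the knowledge questionnaire anonymous. Information retrieval calls it nominal, requires it for CME credits, and reserves anonymity for the attitude questionnaire. An anonymous score cannot be joined to a physician's prescriptions, so the two sections also disagree on whether this covariate can be used at physician level.

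**The case against.** The strongest defence has four parts.

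- **The main result is safe.** This stands in full. The intention-to-treat comparison and its conditional ANCOVA for baseline imbalance use neither variable. A reader might infer that an effective programme could be declared ineffective. That would need a secondary model to displace the main analysis, and nothing in the article suggests it.
- **The covariates are only possible ones.** Statistical analysis describes the regression as a way of exploring which variables affect outcomes, and its examples name neither participation nor knowledge. This lowers the severity. It does not remove the point, because Secondary outcomes names both variables for a between-group adjusted difference and leaves open a choice between models that estimate different things.
- **Adjustment need not remove the effect.** This also stands. A reader might infer that adding attendance wipes out the whole effect. That follows only if attendance means this topic's meeting and the effect acts only in attenders. It is the natural coding for Sardinia, where one arm receives no visit. However, the covariate list is written mainly for the cluster trial: it names PCG size and the two cluster regions, and the questionnaires are described only for that trial. The item is not marked as cluster-only, so Sardinia is not excluded either.
- **New prescriptions may be a baseline measure.** A reader might count them as a third post-randomisation covariate. The text supports only that the window is undated.

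A reader might also infer that non-attenders, lacking a score, would be dropped from the model. The article states no rule for missing scores, so this cannot be asserted.

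**Conclusion.** The point holds for one secondary analysis. Participation and knowledge score are post-randomisation variables named as possible covariates for an adjusted treatment difference. A model that uses them need not estimate the total effect of offering the intervention.

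The size depends on assumptions that the article cannot settle: the share of the effect acting through knowledge, and how participation is coded. For knowledge the result is attenuation in proportion to the mediated share; for participation it ranges from no loss to complete loss. These figures exclude confounding by who attends, which could move the coefficient in either direction, so a bias toward zero should not be taken as certain.

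Severity: should-fix, secondary analysis only.

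**What to change.** - Restrict the adjusted treatment comparison to variables measured before randomisation, such as baseline prescribing, region, PCG size, assisted population and physician age. Take expenditure, polyprescription and the age and sex mix of patients from a pre-randomisation period.
- State that the 12-month window for new prescriptions ends before the intervention.
- Remove participation and the percentage of correct answers from that model. Report them only in a separate analysis labelled exploratory (mediation or dose-response), and define there whether participation means this topic's meeting or any meeting offered.
- Reconcile the two descriptions of the knowledge questionnaire, since the exploratory analysis also needs a score that can be linked to the physician.

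The cost is a change of wording: two covariates leave one model and one window gains a date. No new data are needed, and neither the sample size nor the main analysis changes.

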## Background

Information that doctors receive on benefits and risks of currently used drug treatments generally comes, either directly or indirectly, from the pharmaceutical industry [1-3]. It may thus be unsystematic and biased [4], and may be a component of the (often observed) excessive variability in physicians' prescriptions [5,6], uneasy to explain if one merely looks at evidence-based findings in medical literature.

In recent years the Italian Ministry of Health has made efforts in expanding physicians' access to independent and evidence-based information, like freely distributing the Italian translation of Clinical Evidence and enhancing the quality of the already freely distributed NHS Drug Information Bulletin. Nonetheless, sub-optimal diffusion of independent scientific information is apparent, as well as its comprehensibility to physicians who do not generally have epidemiology and statistics in their medical school background [7-11]. Improving access to, as well as comprehensibility of, evidence-based information remain important goals for Health Authorities, both at national and local levels.

However, simple diffusion of information – even if "evidence-based" – does not seem to affect prescribing behaviour, whereas active interventions like educational outreach visits to doctors (either one to one or small groups meetings), often employing pharmacists, seem more effective especially when clinical information is supplemented by prescribing data, according to an "*audit & feedback*" method [12-16].

Hence, in Italy there is room for improving independent information initiatives, promoting an active outreach system and a different role for NHS pharmacists, the latter being too often confined in administrative/auditing roles. There is also room for improving comprehensibility of medical information, which is infrequently targeted to "average" doctors and hardly ever offered in a clear, direct and appealing fashion, looking at the context of clinical practice [17].

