### Sample size estimates

#### Emilia-Romagna and Friuli Venezia Giulia study (cluster RCT)

From a sample of 40 clusters (about 600 physicians) and using a dedicated software (Cluster Randomisation Sample Size Calculator version 1.0.2, Health Services Research Unit, Aberdeen University) we estimated the intracluster correlation coefficients (ICC) and the sample size that would be required to see a difference of 10% in the prescription of a number of possible drugs (15% for bisphosphonates), assuming an average cluster (PCG) size of 15 (Table 2).

**Table 2 T2:** Estimates of sample sizes to detect a prescribing difference of 10% (with two-tailed test)

	ATC code	Estimate of ICC	Sample size (NCP)
macrolides	J01FA	0.024	68
fluoroquinolones	J01MA	0.030	68
antidepressants	n06ab	0.058	88
nitroderivatives	C01da02, 05,08,14	0.09	96
bifosphosphonates **(15% diff)**	M05ba	0.062	106
proton pump inhibitors	A02BC	0.087	108
phosphomicine	J01xx01	0.014	108
Alfa blockers (for IPB)	g04ca + g04bx49	0.075	116
doxazosin (for IPB)	c02ca04	0.038	128
long acting β2 broncodilators + corticosteroids	R03AK06 e R03AK07	0.092	148
Finasteride +dutasteride	g04cb	0.08	154
opioids	N02A	0.061	164
clarithromicine	J01fa09	0.02	172
esomeprazole	A02bc05	0.023	204
long acting β2 broncodilators	R03AC12 e R03AC13	0.033	208
alendronate	M05ba04	0.08	218
finasteride	g04cb01	0.1	220
salmeterol + corticosteroids	R03ak06	0.102	234
bifosphosphonates	M05ba	0.062	238
azitromicine	J01fa10	0.068	266
risedronate	M05ba07	0	374
norfloxacine	J01ma06	0.055	386
fentanyl	N02ab03	0.043	428
salmeterol	R03ac12	0.053	698
morphine	N02aa01	0.05	2224
buprenorphine	N02ae01	0	Nc
bicalutamide	l02bb03	0	Nc
escitalopram	N06ab10	0	1434
levocetirizine	R06ae09	0.032	>600
antiandrogens	L02bb01+ L02bb03	0	nc

Since we expect to recruit about 150 PCGs we choose for the first round of information meetings the two topics previously described ('drugs for the treatment of benign prostatic hyperplasia', and 'drugs for the primary prevention of osteoporotic fractures in elderly people') because of the clinical relevance of the information to be presented.

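### Within-group variability is fixed as a raw standard deviation, which can fall when prescribing falls proportionally, without GPs becoming relatively more alike

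*Protocol article*

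**What the plan says.** The Secondary outcomes section of the protocol article defines the variability outcome as "difference in the variability (expressed as standard deviations) of prescription of drugs under scrutiny within PCGs (cluster study only". The measure is therefore part of the outcome definition. The article names no relative measure, log scale or adjustment for the mean beside it. It also gives no expected direction for this outcome.

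The Main outcome section puts the effect on a relative scale: "difference (%) in NHS prescription of drugs under scrutiny (expressed as DDD per thousand inhabitants/day". The sample size section works on the same scale, giving "the sample size that would be required to see a difference of 10% in the prescription of a number of possible drugs (15% for bisphosphonates".

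For the main volume indicators a lower level is expected in the informed arm. The 5-alpha-reductase inhibitors should fall, and for alendronic acid and risedronate "a reduced increase is expected for both of these indicators". For two indicators defined as ratios of one drug group to another, an increase is expected.

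The Background gives "excessive variability in physicians' prescriptions" as part of the problem that independent information is meant to address.

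**The concern.** A standard deviation carries the units of the rate. When all values are multiplied by a constant, the SD is multiplied by the same constant. A programme that succeeds on the protocol's own percentage scale can therefore show a lower SD simply because the level is lower. The outcome would then partly repeat the main outcome under another name.

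At stake is a secondary claim that outreach meetings made prescribing within Primary Care Groups (PCGs) more uniform. This is the only listed outcome that addresses spread between prescribers. A reader who recalls the motivation in the Background would naturally take a lower SD as evidence of convergence.

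**Working it through.** **The plan's own figures.** The article states no figure for the variability outcome. The nearest checkable figure is the bisphosphonate sample size. With ICC and cluster size fixed, the number of clusters is proportional to 1/δ², so 238 × (10/15)² = 105.8, against 106 in Table 2. The table behaves as a percentage-effect calculation should.

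**Inputs from the article.** About 150 PCGs ("Since we expect to recruit about 150 PCGs"), taken as 75 per arm. Cluster size 15 ("assuming an average cluster (PCG) size of 15 (Table 2"), or about 2000/150 ≈ 13 GPs from the Abstract. For finasteride plus dutasteride, ICC 0.08 and 154 PCGs.

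**Assumed.** Two-sided α 0.05 and power 80 or 90%; the article says only that the test is two-tailed. Also assumed are the distribution of GP rates, the form of the effect at GP level, and a t-test on PCG-level SDs.

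**Step 1: implied spread.** Table 2 gives no mean, SD or CV, so the CV has to be backed out.
- Design effect = 1 + 14 × 0.08 = 2.12.
- Effective n per arm = (154/2) × 15 / 2.12 = 544.8.
- CV = 0.10 × √(544.8/2) / (1.960 + 0.842) = 0.59 at 80% power, or 0.51 at 90%.
- Within-PCG CV at 80% power = 0.589 × √(1 − 0.08) = 0.565.

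| Drug | CV, 80% power | CV, 90% power |
|---|---|---|
| Alpha blockers | 0.52 | 0.45 |
| Finasteride + dutasteride | 0.59 | 0.51 |
| Alendronate | 0.70 | 0.61 |
| Bisphosphonates | 0.78 | 0.67 |

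The range is about 0.45 to 0.8. Risedronate lies outside it: ICC 0 and 374 PCGs imply 1.34 and 1.16.

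**Step 2: what the SD does under three kinds of response, mean cut 10%.**
- *Every GP cuts 10%.* SD(0.9X) = 0.9 × SD(X). SD ratio 0.90, CV ratio 1.00.
- *Half cut 20%, half do not change.* With mean 1 and within-PCG CV w, the variance becomes 0.82(1 + w²) − 0.81 = 0.82w² + 0.01. At w = 0.565 the SD ratio is √(0.82 + 0.01/0.319) ≈ 0.92, and the CV ratio is 0.92/0.90 ≈ 1.02. Across the CVs simulated, the SD falls by about 6 to 9% while the CV ratio is 1.01 to 1.05. The SD points to convergence while relative spread has widened slightly.
- *Every GP falls by the same absolute amount.* SD ratio 1.00; CV ratio 1/0.9 ≈ 1.11.

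**Step 3: how often a test would pick this up.** Simulated trials of 75 v 75 PCGs with 13 GPs each, CV 0.59, ICC 0.08, lognormal or gamma rates:

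| Response, no relative convergence | SD significantly lower |
|---|---|
| Uniform 10% cut | 36 to 52% |
| Uniform 15% cut | 70 to 87% |
| Half cut 20%, half unchanged | 25 to 35% |
| Equal absolute shift | about 2 to 3% (nominal) |

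With 15 GPs per PCG and lognormal rates, a uniform 10% cut gives 60% at CV 0.40, 45% at 0.55, 30% at 0.75 and 24% at 0.90. Normal rates at CV 0.40 give 92%. The artefact weakens as spread grows, so it would be smaller for risedronate.

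**Step 4: the CV is not neutral.** Under a uniform proportional cut, the CV test stays near its nominal 5%. Under an equal absolute shift of 10% of the mean, it declares significantly more variability in about 75 to 88% of trials.

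**The case against.** The strongest reply is that absolute and relative spread are both legitimate. The Background does not say that excessive variability means relative variability. In DDD per thousand inhabitants/day, GPs who all cut 10% do differ less from one another. That stands, and it is why the SD should stay.

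Second, the artefact depends on how individual GPs respond, and the article does not say. A percentage difference in the main outcome describes arms, not GPs. Under an equal absolute shift the SD behaves correctly. This also stands. Such a shift is a particular pattern, however: for a 10% fall in the mean, a GP at half the mean must cut 20% and a GP at twice the mean only 5%. Nothing in the article suggests it. Conversely, a uniform cut is an extreme case, because the intention-to-treat analysis includes GPs who do not attend. The mixed response in the working allows for that and leaves a reduced but real risk.

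Third, the article announces no direction or claim for this outcome, variability is not among the Objectives, and the main outcome will show the change in level alongside. This limits the weight of the point without removing it.

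A reader might infer that the SD must follow the mean, so that success will inevitably be reported as reduced variability, or that the CV should replace the SD. The documents support neither: they give no means, SDs or GP-level effect form, and the CV errs in the opposite direction under an absolute shift.

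**Conclusion.** The point holds as a minor one. For volume indicators where lower prescribing is expected, a raw SD alone cannot tell a proportional or mixed reduction from convergence of practice. At a GP-level CV of about 0.59, a uniform 10% cut would give a significantly lower SD in roughly 35 to 50% of trials with no relative convergence. If only half the GPs respond, at the same mean cut, the figure is 25 to 35%.

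These figures rest on the back-calculated CV, on skewed GP rates and on a t-test of PCG-level SDs. The 0.59 is not printed in Table 2 and falls to 0.51 at 90% power. Under an equal absolute shift there is no artefact in the SD. If the SD is also applied to the ratio indicators, the artefact runs the other way, and success could look like greater variability.

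One secondary outcome of the cluster trial is affected. The main outcome and the sample size are not.

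**What to change.** Keep the within-PCG SD. Add the within-PCG coefficient of variation, or the SD of log prescribing, compared between arms at PCG level. Present both beside the change in mean, and claim reduced variability only if both fall.

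In the scenarios simulated without true convergence, this rule kept false claims at or below about 2.5%. It detected a true 15% convergence in at least 95% of trials at CV 0.59 when the mean also fell by 10% (SD ratio 0.85 × 0.90 = 0.765). If the mean does not change, the SD ratio is only 0.85, the same as for a 15% proportional cut. The SD test, and so the joint rule, then detects it in no more than about 70 to 87%.

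The cost is one more secondary analysis, a sentence of wording and a slightly stricter criterion. No new data are needed.

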**Methods/Design:**

Two RCTs are planned:

1) a two-arm cluster RCT, carried out in Emilia-Romagna and Friuli Venezia Giulia, will evaluate the effectiveness of small group meetings, randomising about 150 Primary Care Groups (corresponding to about 2000 GPs) to pharmacist outreach visits on two different topics. Physicians' prescriptions (expressed as DDD per 1000 inhabitants/day), knowledge and attitudes (evaluated through the answers to a specific questionnaire) will be compared for target drugs in the two groups (receiving/not receiving each topic).

2) A three-arm RCT, carried out in Sardinia, will evaluate both the effectiveness of one-to-one meetings (one pharmacist visiting one physician per time) and of a 'new' information format (compared to information already available) on changing physicians' prescription of specific drugs. About 900 single GPs will be randomised into three groups: physicians receiving a visit supported by "traditional" information material, those receiving a visit with "new" information material on the same topic and those not receiving any visit/material.

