## Discussion

The two proposed RCTs will let us better understand the potential usefulness of NHS pharmacists assuming a more active role in transferring evidence-based information to physicians. Besides data on prescribing impact, the studies will provide qualitative insight on the feasibility of such information programs, with special attention to how different organizational settings in different regional areas may lead to better or worse implementation. As already said, these studies represent an unprecedented effort to accomplish such evaluations on quite a large scale and in a 'natural' organizational setting, which would be minimally altered by the interventions themselves. Moreover, the two RCTs will test two different strategies of information delivery: using small groups or one to one meetings. While these strategies will not be directly compared (being not employed in the same study but in two different ones), their feasibility and impact will be critically evaluated, also in light of other experiences described in the scientific literature and of methods used by the pharmaceutical industry to bring information to doctors on a large scale.

Last but not the least, the role of the format of medical information will be investigated: this could be a critical part in the implementation of information programs and its importance may be often underestimated, considering that medical schools generally do not offer the necessary tools to unscramble data published in the scientific literature; that average doctors do not have enough time to select and read what may add relevant information to their knowledge; and that, eventually, the uptake of this information may be facilitated by offering it in a clear, direct and appealing fashion, looking at the context of clinical practice [17].

As usually happens, the evaluation of complex interventions is intricate given the many different variables into play: it is the other side of the pragmatic nature of these RCTs, which is also, and undoubtedly, one of their strengths. Moreover, the ambitious quantitative hypothesis to be tested (10 or 15% difference in doctors' prescriptions) will not be easily demonstrated, in spite of the involvement of about 2000 physicians in the cluster RCT and about 900 in the single doctors RCT: an even larger sample size would have been necessary to see smaller but still relevant prescribing differences.

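### The 15% osteoporosis sample size is for the bisphosphonate class, not the two drugs named as main indicators; with about 150 PCGs, 10% is out of reach for both drugs and 15% for risedronate

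*Protocol article*

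**What the plan says.** The indicators for the first two topics follow the list of secondary outcomes in the protocol article. For osteoporosis, "the main indicators will be: difference in the prescription of either alendronic acid or of sodium risedronate". These are two separate indicators, since "a reduced increase is expected for both of these indicators, especially for the latter", the latter being risedronate. The osteoporosis secondary indicators are raloxifene, strontium ranelate and a ratio of alendronic acid to the other oral bisphosphonates. Total bisphosphonate prescribing is in neither list.

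The cluster trial's sample size section sets the target as a "difference of 10% in the prescription of a number of possible drugs (15% for bisphosphonates"). The calculations were made by "assuming an average cluster (PCG) size of 15" GPs. The heading of Table 2 reads: "Estimates of sample sizes to detect a prescribing difference of 10% (with two-tailed test"). Its osteoporosis rows are:

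- bisphosphonates (M05BA) at 15%: ICC 0.062, 106 PCGs
- bisphosphonates (M05BA) at 10%: ICC 0.062, 238 PCGs
- alendronate: ICC 0.08, 218 PCGs
- risedronate: ICC 0, 374 PCGs

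Directly after the table comes: "Since we expect to recruit about 150 PCGs we choose for the first round of information meetings the two topics previously described", with clinical relevance as the reason for the choice. The Abstract describes the trial as "randomising about 150 Primary Care Groups (corresponding to about 2000 GPs"). The Discussion refers to "the ambitious quantitative hypothesis to be tested (10 or 15% difference in doctors' prescriptions"), says it will be hard to demonstrate, and adds that a still larger sample would have been needed for smaller differences.

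**The concern.** The outcome that was sized is not an outcome that will be tested. The 15% allowance appears in Table 2 only for the class total, and that is the only osteoporosis row below 150 PCGs. The two drugs that serve as main indicators have rows only at 10%, and both exceed 150.

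A reader who takes the sample size paragraph and the Discussion together will conclude that differences of 10% (15% for bisphosphonates) are within reach on the main indicators, and that only smaller ones are not. For risedronate neither figure is reached, yet this is the drug on which the plan expects the clearer effect. A non-significant risedronate result could then be taken as evidence that the visits do not work, when an effect of the size hoped for would still be compatible with the data.

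**Working it through.** **Inputs.** From Table 2: 238 and 106 PCGs for M05BA at 10% and 15%; alendronate 218 (ICC 0.08); risedronate 374 (ICC 0); finasteride+dutasteride 154 (ICC 0.08); 15 GPs per PCG. About 150 PCGs expected (sample size section) and about 2000 GPs (Abstract).

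**Assumptions.** N is read as the total over both arms: every exact entry is even, and the text sets the figures against about 150 PCGs. Alpha and power are not stated. They enter only step 4, where two-sided 5% and either 80% or 90% are assumed.

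**1. Scaling rule, checked on the plan's own figures.** With ICC and cluster size fixed, N is proportional to 1/(difference)². For the class, 238 × (10/15)² = 105.8, and the table prints 106. The rule reproduces. The 218 and 374 themselves cannot be rebuilt, because no means, standard deviations or power are given.

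**2. The named drugs at 15%, 15 GPs per PCG.**
- Alendronate: 218 × 4/9 = 96.9, so 97-98 PCGs. Below 150.
- Risedronate: 374 × 4/9 = 166.2, so about 167 PCGs. Above 150.

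**3. Detectable difference with 150 PCGs at the table's own power** = 10% × √(N/150).
- Alendronate: 10% × √(218/150) = 12.1%
- Risedronate: 10% × √(374/150) = 15.8%
- Finasteride+dutasteride: 10% × √(154/150) = 10.1%

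**4. Power with 150 PCGs** = Φ[(1.96 + z_power) × (difference/10%) × √(150/N) − 1.96], for table power 80% (90% in brackets).

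| | 10% difference | 15% difference |
|---|---|---|
| Alendronate | 64% (77%) | 94% (98%) |
| Risedronate | 43% (54%) | 76% (87%) |

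**5. Cluster size.** 2000/150 = 13.3 GPs per PCG, not 15. The PCG count is multiplied by [(1 + (m−1)·ICC)/m] ÷ [(1 + 14·ICC)/15] with m = 13.33.
- ICC 0.08: (1.987/13.33) ÷ (2.12/15) = 1.054
- ICC 0: 15/13.33 = 1.125

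| | PCGs at 10% | PCGs at 15% | Detectable with 150 PCGs |
|---|---|---|---|
| Alendronate | 218 × 1.054 = 230 | 96.9 × 1.054 = 102 | 12.4% |
| Risedronate | 374 × 1.125 = 421 | 166.2 × 1.125 = 187 | 16.8% |
| Finasteride+dutasteride | 154 × 1.054 = 162 | – | 10.4% |

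**6. The other prostate indicator.** The second main indicator for benign prostatic hyperplasia is a ratio of terazosin plus tamsulosin to alfuzosin plus doxazosin. Table 2 has rows for alpha blockers as a group (116) and for doxazosin (128), but none for this ratio.

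**The case against.** The strongest reply is that 218 and 374 are 10% figures, while the text relaxes the target to 15% for bisphosphonates. A reader might infer from those two numbers that the 10 or 15% target is missed for both drugs. The documents do not support that. By the table's own scaling, alendronate at 15% is covered with a clear margin, and remains so at 13.3 GPs per PCG.

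At 15% the risedronate shortfall is also modest: about 167 PCGs against about 150, or 76% power instead of 80%. Since the plan expects more effect on risedronate, 10% is arguably not the figure to judge it by. Both points stand, and they lower the severity.

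The figures are also printed openly, the target is called ambitious, and the topics were chosen for clinical relevance. This stands only in part. Saying that a larger sample is needed for smaller differences still implies that 10 or 15% is attainable on the indicators used.

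The 13.3 is a ratio of two rounded numbers, while 15 agrees with the pilot sample (600 physicians in 40 clusters). That is fair, and the correction changes no conclusion: risedronate misses 15% and alendronate meets it with either cluster size. The ICC of 0 for risedronate was estimated from data, and four other rows also show 0, so it is not an error. It is simply the most favourable non-negative value.

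Finally, 154 against about 150 for finasteride+dutasteride is within rounding and is not a shortfall worth raising.

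**Conclusion.** The point holds in limited form. The 15% sample size for osteoporosis belongs to a class total that is neither a main nor a secondary indicator. For the two main indicators, with about 150 PCGs:

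- 10% is not reached for either drug.
- 15% is reached for alendronate.
- 15% is not reached for risedronate, modestly so at 15 GPs per PCG and more clearly at 13.3.

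No printed figure is shown to be miscalculated, and a blanket claim that the trial misses its target would go too far. The PCG counts and detectable differences rest on reading Table 2 as totals over both arms and on the table's own ICCs. They do not depend on the unstated alpha or power. A true risedronate ICC above 0, with the same standard deviation, would make its position worse. This should be fixed because it governs how a null risedronate result is read; it does not invalidate the design.

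**What to change.** Restate the cluster trial's sample size paragraph for the indicators actually named, giving the difference detectable with about 150 PCGs at the power used for Table 2, and state that power:

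- alendronate: about 12.1% (12.4% at 13.3 GPs per PCG)
- risedronate: about 15.8% (16.8%), and larger if its true ICC is above 0
- finasteride+dutasteride: about 10.1% (10.4%)

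Add that the 106 PCGs at 15% refer to the bisphosphonate class, that no sample size supports the alpha-blocker ratio, and that a null result on risedronate does not rule out an effect of 10-15%.

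The cost is wording and a few restated figures, with no extra recruitment. The downside is that the stated detectable differences become less favourable. Making the whole class the main indicator would also align outcome and sample size, but it changes a primary indicator. That is a design choice for the sponsor and is not required.
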